**LIST OF ABBREVIATIONS AND RELEVANT DEFINITIONS**

Ach Acetylcholine

AIx Augmentation index

BMI Body mass index

BP Blood pressure

CAM Cellular adhesion molecules

CC Compliance coefficient

CCMO Central Committee on research Involving Human Subjects

CRP C-reactive protein

DC Distensibility coefficient

ED Endothelial dysfunction

EF Endothelial function

(F)FA (Free) Fatty acids

FMD Flow-mediated dilatation

Hb Hemoglobin

HF High-fat

IC Informed consent

IMP Investigational Medicinal Product

IMT Intima-media complex thickness

METC Medical ethical commission (in Dutch: medisch ethische commissie)

PBMC Peripheral blood mononuclear cells

Pwv Pulse wave velocity

Q-PCR Quantitative real time polymerase chain reaction

(S)AE (Serious) Adverse Event

SFA Saturated fatty acids

Sponsor The sponsor is the party that commissions the organization or performance of the research, for example a pharmaceutical company, academic hospital, scientific organization or investigator. A party that provides funding for a study but does not commission it is not regarded as the sponsor, but referred to as a subsidizing party

TAG Triacylglycerol

vWF Von Willebrand factor

WMO Medical Research Involving Human Subjects Act (In Dutch: Wet Medisch-Wetenschappelijk Onderzoek met Mensen)

YEM Young’s elastic modulus

**SUMMARY**

**Rationale:**

Endothelial dysfunction (ED) is a hallmark for the initial stage of vascular dysfunction and has been associated with diet-related disorders such as cardiovascular disease. This makes prevention of ED an important health target. From previous studies we know that a high-fat (HF) meal (challenge) impairs postprandial endothelial function (EF). Current studies only evaluated the effect of a HF meal on Flow Mediated Dilatation (FMD), a measure of macro vascular EF. This methodology (FMD) however, is time consuming and large variations in reproducibility are reported in literature. The question remains whether other types of macro- and micro vascular EF measurements can be used to observe ED after a HF meal that are more accurate, faster and easier to perform. In addition, it is know that the postprandial phase results in activation of leukocytes. This activation of leukocytes is likely to contribute to ED, but the exact underling mechanism remains unclear.

**Objectives:** The primary objectives are formulated, to evaluate the effect of a HF meal on EF on both, macro- and micro vascular level by evaluating different measures for EF. This will be performed with the ultimate goal to establish a reliable model to evaluate HF meal induced ED, which can be used in further studies. Our secondary objectives are to elucidate the underling mechanisms of HF meal-induced ED and to identify early biomarkers of ED.

**Study design and study population:** Double-blind cross-over intervention with 20 healthy Caucasian men (age 18-30, 18<BMI<25)

**Intervention:** Each participant will consume a HF milkshake or a ‘control’ milkshake (comparable with a normal breakfast) after overnight fasting.

**Study outcome**: The primary study outcomes are the functional measurements on macro-and micro vascular function before and 3 and 6 hours after a HF meal. Our secondary study outcomes are peripheral blood mononuclear cells (PBMC) gene expression profiles, white blood cell activation markers, plasma cytokine profiles and other plasma markers of endothelial function before and after a HF challenge. These findings will thereafter be correlated with the outcome of the functional measurements.

**Nature and extent of the burden and risks, benefit and group relatedness:** During a screening visit 3 ml blood will be drawn and urine will be collected after a overnight fast and body weight and length will be measured. A general and medical questionnaire will be used. During the study each participant will consume a milkshake containing 95 grams of fat or a ‘control’ milkshake after a overnight fast. Both interventions will be performed in triplicates and all 6 testing days are randomly divided over a 15 week period. Functional measurements of ED will be performed at baseline and 3 and 6 hours after the intervention. At baseline (-1.5 hours) and 1,2,3,5 and 6 hours after the intervention, blood will be collected by using a venflon. The total amount of blood will be 192 ml per day. Hb values of each participant will be monitored during the study to be sure that blood collection will not lead to anaemia. The time investment requested from the participants is 1.5 hours at the information meeting, 0.5 hours at a screening session, and 6 x 9 hours during the intervention days. The risks associated with venous blood drawing using the venflon technique are minimal. The consumption of the milkshake is not expected to be associated with discomfort and all performed functional measurements of ED are non-invasive and risks are therefore minimal.

**1. INTRODUCTION AND RATIONALE**

**1.1 Scientific relevance**

The endothelium is a thin layer of cells that lines the interior surface of the blood vessels. The endothelium responds to changes in the physical, metabolic, and inflammatory environment and by doing this, it maintains vascular homeostasis in the arteries and in the microcirculation. Endothelial dysfunction (ED) is a hallmark for the initial stage of vascular dysfunction1 and has been associated with several diet-related diseases2. As nicely reviewed by Khazaei *et al.* 3, several studies support the hypothesis that reduction of endothelial dysfunction may lead to reduced cardiovascular morbidity and mortality (e.g. heart disease, stroke). This makes prevention of ED an important health target.

From previous studies we know that nutritional challenges result in an impaired postprandial endothelial function (EF) as measured by flow-mediated dilatation (FMD), markers of inflammation and markers of oxidative stress4-9. These effects are reversible and temporally. A high-fat (HF) challenge, with a fat content between 80-100g, has the strongest and most clear effect on EF compared to other nutritional challenges4, 10.

**1.2 Functional measures of endothelial function**

EF can be assessed by several methodologies/functional measurements of which each has its own advantages and drawbacks. Currently, HF meal induced ED is only studied on a macro vascular level by using FMD. Flow mediated dilatation is a commonly used technique to investigate the ability of vascular endothelial cells to respond to changes in shear stress. However, this technique is time consuming and large variations in reproducibility are found in the literature (reviewed by De Roos *et al*. 2003 11).

There are other methodologies to monitor EF besides FMD, although these are not applied to monitor HF meal induced ED. Another way to (indirectly) indicate EF on macro vascular level is by measuring the arterial stiffness12. Arterial stiffness (i.e. impairment of the cushioning capacity) leads to an increase in systolic blood pressure and can be estimated by quantifying pulse pressure, but is better described by distensibility and compliance coefficients, pulse wave velocity and wave reflection. It is also possible to monitor EF on a micro vascular level. Abahji *et al.* (2006)13 observed impaired micro vascular EF after acute hyperhomocysteinemia by using ionthophoresis techniques. The question remains if these other methodologies are also applicable to observe a HF meal induced ED.

**1.3 Elucidation of how a high-fat meal can induce endothelial dysfunction**

So far, it is not completely known how a HF meal results in a impaired EF. However, it is known that triglycerides and markers of inflammation are increased during a postprandial response4, 10. In addition, van Oostrom *et al.* (2004) observed an increased expression of activation markers on several white blood cells, including neutrophiles and monocytes, after a HF challenge. These activation markers (CD11A, CD11B and CD62L) are known to interact with the endothelium10. Postprandial activation of white blood cells may therefore result in an increased adhesive capacity of these cells to the endothelium. This might have an negative effects on EF, since prevention of adherence of leukocytes to the endothelium results in preservation of EF14. Evaluating these and other white blood cell activation markers during a HF postprandial response, may give information about of the role of activated blood cells in postprandial ED.

Several factors are likely to be important precursors of ED, but the precise relationship betweenthese factors and ED is still poorly understood and reliable early biomarkers are lacking. In humans, EF is now assessed biochemicallyby measuring circulating levels of oxidative products and markers of endothelial activation and inflammation. Important markers in this respect are NO, NOx, prostacyclin, cyclic adenosine monophosphate, cyclic guanosine monophosphate, cytokines, endothelin, intercellular adhesion molecule-1 (ICAM-1), vascular cell adhesion molecule-1 (VCAM-1), von Willebrand factor, plasminogen activator inhibitor-1, or thrombomodulin. Information about changes in PBMC gene expression profiles and plasma cytokine profiles during postprandial ED could lead to novel early biomarkers of ED and may provide us with leads for possible mechanisms.

**1.4 Study aim**

In the current study, we aim to evaluate the effect of a HF meal on EF on both, macro- and micro vascular level by evaluating different measures for EF. This will be performed with the ultimate goal to establish a reliable functional measure for HF meal induced ED, which can be used in further studies. Local and regional arterial stiffness and macro vascular blood flow will be evaluated in order to observe an effect on macro-vascular level and micro vascular blood flow will be evaluated to observe an effect on micro-vascular level. Comparison of these measures will allow us to establish the most accurate but also easy and fast method for monitoring HF meal induced ED.

In addition we aim to obtain more knowledge on the underling mechanisms of HF meal-induced ED and to identify early biomarkers for ED. In order to do so we will investigate HF meal-induced changes in gene expression profiles of peripheral blood mononuclear cells (PBMC), activation markers of white blood cells, plasma cytokine profiles and other markers of EF (see paragraph 1.4). These findings will thereafter be correlated with the outcome of the functional measurements to obtain possible leads for biomarkers and mechanism.

**2. OBJECTIVES**

The objectives are formulated to investigate the effect of a HF meal on EF. The primary objectives are to evaluate the effect of a HF meal on several measures of macro- and micro vascular EF. Our secondary objectives are to obtain more knowledge on the underling mechanisms of HF meal-induced ED and to identify early biomarkers of ED.

**2.1 Research questions and hypothesis**

1. Does a HF meal have an effect on EF that can be measured with several measures of micro- and macro-vascular function and which of these methodologies is best applicable to measure HF meal induced ED?

 *Both micro- and macro-vascular endothelial function will be affected after a HF meal. All used methodologies can therefore be used for measuring HF induced ED, although some might be more applicable (more accurate, easier to use).*

1. Does a HF meal results in changes in PBMC gene expression profiles, white blood cell activation markers, plasma cytokine profiles and other markers of ED and can these observed effects be correlated to the functional measurements of ED?

 *A high fat challenge will have an effect on PBMC gene expression profiles, white blood cell activation, plasma cytokine profiles and other plasma markers of ED. Some of these changes will correlated either positively of negatively to the outcomes of the functional measurements and might be good candidate early biomarkers for ED and will provide us with leads for a possible mechanism.*

**3. STUDY DESIGN**

**3.1 Intervention study**

This study is a double-blind cross-over intervention (challenge) study, planned to run (incl. a 2 week break during Christmas/ new year) from 20-10-2008 till 15-02-2009. A total of 20 healthy male individuals will receive a) a milkshake containing 95g of fat (high-fat challenge) or b) a milkshake containing the same nutritional and energetic value of an average breakfast (based on ‘voedselconsumentenpeiling’ 2003 from TNO). Data obtained with this ‘control’ milkshake will not directly be compared to the HF milkshake, but will be used to obtain knowledge about normal circadian rhythms in EF. Both interventions will be performed in triplicates, to obtain information on variation in the different measures of EF and the variation in PBMC gene expression, white blood cell activation markers, plasma cytokine profiles and other plasma markers of ED. This means that each individual will visit the department on 6 different days. All testing days will be randomly divided over the study time period, with a minimal period between the testing days of 7 days, in order to exclude carry over effects. Randomization is performed in which only the variants ABABAB and BABABA are possible. Two participants will be evaluated on each testing day (see paragraph 6.2.4)

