**8. STATISTICAL ANALYSIS**

To observe an effect of HF on EF, changes in primary outcome variables will be tested using repeated measures ANOVA (mixed model) using pre-defined contrasts, i.e. 3 versus 0 hrs and 6 versus 3 hrs. ANOVA will also be used to quantify the within- and between subject variation of the various measurements.

Changes in secondary outcome variables will be tested using repeated measures ANOVA (mixed model) using pre-defined contrasts, i.e. 3 versus 0 hrs and 6 versus 3 hrs. Additionally, incremental areas under the curve will be calculated for all significant altered secondary outcome variables using the trapezoïdal rule and compared between meals using one-way ANOVA. All statistical analysis will be performed with SPSS version 15.0.

Data analysis of the microarrays will be performed using a Bayesian linear regression model (implemented in the software package LIMMA; [www.bioconductor.org](http://www.bioconductor.org/)). Raw microarray data will be normalized using RMA quantile normalization. Statistically significant changed genes will be identified by student paired t-test followed by a false discovery rate correction (FDR) The latter is used to correct for multiple testing.

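### For the primary outcomes, the high-fat meal is tested only by change over the day and not against the control days, so a time-of-day change could be read as a meal effect

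*Protocol*

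**What the plan says.** Section 2 sets a question about the meal: "The primary objectives are to evaluate the effect of a HF meal on several measures of macro- and micro vascular EF". The Summary defines the primary outcomes as the "functional measurements on macro-and micro vascular function before and 3 and 6 hours after a HF meal".

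Section 3.1 describes a randomised cross-over in which each man has three high-fat and three control days, in the order ABABAB or BABABA. It then states that the control data "will not directly be compared to the HF milkshake, but will be used to obtain knowledge about normal circadian rhythms in EF".

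Section 8 opens: "To observe an effect of HF on EF, changes in primary outcome variables will be tested". The tool is a repeated measures mixed model, with 3 versus 0 h and 6 versus 3 h as the pre-defined contrasts. No meal term or meal-by-time term is named. Secondary outcomes get the same time contrasts, but for those found significantly altered the incremental areas under the curve are then "compared between meals using one-way ANOVA".

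Section 6.2.4 (Tables 2 and 4) puts the functional measurements at 7.30, 12.00 and 15.00 for the first participant of the day and 1.5 h later for the second.

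**The concern.** On a high-fat day, the 3 h reading always comes 4.5 hours later on the clock than baseline, and the 6 h reading three hours after that. A time contrast within those days is the sum of the high-fat effect and whatever endothelial function does over the same hours for other reasons. The protocol itself expects such a daily rhythm and gives it as the purpose of the control days. It thus names the confounder and collects the data that could remove it, but excludes those data from direct comparison.

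A significant 3 h contrast would then not by itself answer the primary objective. The study's wider goal is also exposed: a measure that drifts over the day could be chosen as a sensitive marker of meal-induced dysfunction. Separately, Sections 3.1 and 8 disagree on whether the meals are compared at all.

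**Working it through.** **1. The plan's own figures (Section 4.4).** Two-sided paired t-test, alpha 5%, noncentral t distribution (two-sided is assumed; the protocol does not say).
- Iontophoresis: 3 units, SD 4.5 taken as the SD of the paired difference, n = 20. Power is 80.7%, so the planned 80% reproduces.
- FMD: 6 FMD%, SD of a change = 2.8 × √2 = 3.96. The smallest n for 90% power is 7, as stated.

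The FMD calculation is explicitly before versus after the fat load. Neither calculation mentions a high-fat versus control difference.

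**2. What the time contrast estimates.** Let M be the meal effect at 3 h and C the change from baseline to 3 h that would occur without it. The within-high-fat contrast estimates M + C. High-fat change minus control change estimates M relative to the control shake, because C appears in both terms and cancels.

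**3. How often a null meal looks positive.** Set M = 0. The protocol gives no value for C, so 1, 1.5 and 2 FMD% are assumptions. n = 20, two-sided 5%.
- One high-fat day: SD of change 3.96.
- Three days averaged: SD = 3.96 × √(r + (1 − r)/3), where r is the correlation between changes on replicate days. r is not in the protocol; 0 and 0.3 are assumed. The SD is 2.29 at r = 0 and 2.89 at r = 0.3.

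| Assumed drift (FMD%) | One day | Triplicate, r = 0 | Triplicate, r = 0.3 |
|---|---|---|---|
| 1 | 19% | 46% | 31% |
| 1.5 | 36% | 80% | 60% |
| 2 | 57% | 96% | 84% |

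Replication raises these rates because drift is a bias, not noise. All three drifts are well below the 6 FMD% used in Section 4.4.

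**4. Power of the between-meal contrast.** Iontophoresis, 3 units, n = 20, 4.5 taken as the SD of a one-day change, three days per meal averaged.
- Correlation only between days of the same meal: SD = √(2 × 20.25 × (r + (1 − r)/3)). At r = 0 the SD is 3.67 and power 93%. At r = 0.3 the SD is 4.65 and power 78%.
- One correlation common to all six days: SD = 4.5 × √(2(1 − r)/3). At r = 0 the SD is again 3.67 and power 93%. At r = 0.3 the SD is 3.07 and power about 98%.
- Like-for-like comparator, the triplicate within-high-fat test: SD = 4.5 × √(r + (1 − r)/3). At r = 0 the SD is 2.60 and power 99.8%. At r = 0.3 the SD is 3.29 and power 97%.

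**The case against.** The authors saw the circadian issue and collected control days for it, so those days could inform interpretation. They also serve the stated aim of quantifying variation. This stands in part. A reader might infer that a drift would be reported as a meal effect, or that the control data are wasted. The text supports neither: it supports only that a drift could be so read, since no rule says how the control pattern adjusts or qualifies the high-fat result.

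A reader might also infer that the two meals are never compared. That fails for the secondary outcomes, where Section 8 plans a between-meal comparison of areas under the curve. Nor does Section 8 say which days enter the primary model. That half of the participant-days stay out of it is a likely reading of Section 3.1, not a stated fact. Nothing in the protocol says that repeating the cuff occlusion or iontophoresis shifts later readings, so the point does not rest on that.

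The between-meal contrast also has limits. Table 1 shows shakes that differ in energy (3992 versus 1674 kJ), protein (6.13 versus 17 g) and carbohydrate (22.31 versus 49.7 g) as well as fat (94.83 versus 14.5 g). Section 1.1 says that nutritional challenges in general impair postprandial function, so the control shake may move the outcome too, and subtracting it may remove part of the effect. This changes what is estimated, but it does not let the time contrast separate meal from hour.

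Finally, it is tempting to call the change free by setting its power against the planned 81%. That compares a triplicate contrast with a one-day test. Like for like, power falls from 99.8% to 93% with uncorrelated days. At correlation 0.3 it goes from 97% to 78% if days correlate only within a meal, but does not fall if the correlation is common to all days (about 98%).

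**Conclusion.** The point holds for the primary outcomes. The objective is the effect of the meal, the stated contrasts confound it with time of day, and Section 3.1 expressly excludes the direct comparison that would separate them. That exclusion is explicit, so it is not a detail left to a later analysis plan. Sections 3.1 and 8 also conflict over comparing the meals.

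The size depends on a drift that the protocol does not give. At 1 to 2 FMD%, false-positive rates run from 19% to 57% with one day and from 31% to 96% with triplicates averaged at correlations of 0 to 0.3, against a nominal 5%. Twenty men remain near or above the planned 80% power for the between-meal contrast under the assumptions shown, the lowest figure being 78%.

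**What to change.** In Section 3.1, delete the statement that excludes a direct comparison with control; this also removes the conflict with the secondary analysis. In Section 8, make the primary test the meal-by-time contrast in the mixed model: high-fat change minus control change, for 3 h versus baseline and for 6 h versus 3 h, accounting for participant and repeated test days. Report the within-high-fat change as supportive. Restate in Section 4.4 that 20 men are judged on this contrast, with the assumed correlation between days.

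The cost is wording only, with no added visits or samples. Precision may be lost relative to the triplicate within-high-fat test. The estimand becomes high-fat shake versus ordinary breakfast shake, and the report should say that the two differ in more than fat.

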**5. INTERVENTION**

**5.1 Intervention meals**

Each participant will receive a high-fat challenge or a ‘control’ meal. The HF meal will consist of a milkshake, containing a total amount of 95g of fat (consisting of mainly saturated fatty acids) and the total volume that will be consumed is 500ml. The ‘control’ meal will consist of a milkshake of witch the content can be compared to a normal breakfast. Both shakes/meals should be consumed within 10min. Table 1 describes the ingredients, macronutrient composition and total energy intake for each shake/meal.

**Table 1:** *A)**Ingredients used for both milkshakes and B) Nutritional values of the two milkshakes according to Nevo2006.*

A)

| HF milkshake | ‘control’ milkshake |
| --- | --- |
| 53% Whipped cream  3% Sugar  44% Water | 42% full cream milk  47% full cream yoghurt  10% lemonade  1% wheat fiber |

**B)**

|  | HF milkshake (500ml) | ‘control’ milkshake (500ml) |
| --- | --- | --- |
| Energy (KJ) | 3992.08 | 1674.00 |
| Protein (g) | 6.13 | 17.00 |
| Fat (g)  Of which saturated (g) | 94.83  54.22 | 14.50  9.00 |
| Carbohydrates (g) | 22.31 | 49.70 |
| fiber (g) | 0 | 2.30 |

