**6.2.4 Intervention**

Participants will be asked to check in 30 min prior to the first data collection point (T=-2h) in order to be sure that measurements are taken at a ‘resting’ state. Before the start of each study day, the Hb value of each participant will be determined by using a hemoglobin analyzer (HemoCue 201). Participants with a Hb value below 8.4 mmol/L will not be measured and are asked to make a new appointment. If Hb values are normal (e.g. above 8.4mmol/L), a venflon will be placed into the antecubital vein of the participant’s forearm by qualified and experienced personnel. Functional measurements will be performed at baseline (T= -1.5h) and 3 and 6 hours after the intervention. The total time required for the functional measurements is set at 1.5 hours in total and the protocol is as followed:

- 15 min prior to the measurements, participants are asked to lie down on the bed
- Blood pressure will be measured (required for some measures below)
- Macro vascular regional arterial stiffness will be assessed by tonometry
- Macro vascular local carotid arterial stiffness will be assessed by ultrasound
- Macro vascular blood circulation will be assessed by FMD/ ultrasound
- Micro vascular blood circulation will be assessed by iontophoresis

Blood will be collected at baseline (T=-1.5) and 1, 2, 3, 5, and 6 hours after the intervention. An overview of the data collection points on each study day is shown in table 2.

**Table 2:** *protocol on each study day. NB. Data will be collected for two participants each day. The second participant will receive the same protocol, only all time points are delayed by one and a half hour.*

| Intervention time, after overnight fasting (in hours (h)) | -1.5h | 0h | 1h | 2h | 3h | 5h | 6h |
| --- | --- | --- | --- | --- | --- | --- | --- |
|  | (7.30am) | (9.00am) | (10.00am) | (11.00am) | (12.00am) | (14.00am) | (15.00am) |
| Consumption of the test meal |  | X |  |  |  |  |  |
| **Primary measurements** |  |  |  |  |  |  |  |
| Macro vascular:  Arterial stiffness  by tonometry | X |  |  |  | X |  | X |
| by ultrasound | X |  |  |  | X |  | X |
| Flow mediated dilatation | X |  |  |  | X |  | X |
| Micro vascular:  Iothophoresis | X |  |  |  | X |  | X |
| **Secondary measurements** |  |  |  |  |  |  |  |
| Total blood sampling (ml) | 56 |  | 8 | 8 | 56 | 8 | 56 |
| PBMC gene expression |  |  |  |  |  |  |  |
| By microarray analysis | X |  |  |  | X |  | X |
| By Q-PCR | X |  | X | X | X | X | X |

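### The control days cannot show circadian rhythm in endothelial function, because each one includes a breakfast shake before both later measurements

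*Protocol*

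**What the plan says.** Section 3.1 describes a cross-over with two conditions, the HF shake and the control shake, each given on three days in one of two alternating sequences. It says that data from the control "milkshake will not directly be compared to the HF milkshake" but "will be used to obtain knowledge about normal circadian rhythms in EF". It also says that both meals are given in triplicate to learn about variation in the measures, so the control days have a second stated use.

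Section 5.1 defines the control: "The ‘control’ meal will consist of a milkshake of witch the content can be compared to a normal breakfast". Table 1 gives it 1674 kJ, 17 g protein, 14.5 g fat (9 g saturated) and 49.7 g carbohydrate.

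Table 2 in Section 6.2.4 puts the test meal at 0 h and the functional measurements at -1.5 h, 3 h and 6 h, after an overnight fast. Two participants are measured per day. On the later of the two slots it says: "The second participant will receive the same protocol, only all time points are delayed by one and a half hour".

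Section 1.1 gives the protocol's own premise about meals: "nutritional challenges result in an impaired postprandial endothelial function (EF". It calls the high-fat challenge the strongest of these, which does not mean that other meals have no effect.

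**The concern.** To learn about time of day from repeated measurements, one needs either unfed days or some other way to hold the meal effect apart. Here only the baseline is unfed. From baseline to 3 h and 6 h the clock advances and the participant goes from fasted to fed, together and on every control day.

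Two misreadings follow. A fall in EF after the control shake could be reported as normal rhythm when it is a response to breakfast. A flat profile could be reported as no rhythm when a rise through the morning has been offset by a meal-induced fall. What is at stake is the interpretation of half the study days (three of six per participant).

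**Working it through.** **Inputs.** Table 1 (Section 5.1): energy row "Energy (KJ) | 3992.08 | 1674.00" and carbohydrate row "Carbohydrates (g) | 22.31 | 49.70", with HF first and control second; fat 94.83 g and 14.50 g; protein 6.13 g and 17.00 g; fibre 0 g and 2.30 g. Table 2 (Section 6.2.4): meal at 0 h, EF at -1.5, 3 and 6 h. Section 3.1: two conditions only.

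**1. Is the control a real meal?** Energy is recomputed with assumed factors of 17 kJ/g for protein and carbohydrate, 37 kJ/g for fat and 0 to 8 kJ/g for fibre.

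- Control: 17 × 17 + 49.7 × 17 + 14.5 × 37 = 289 + 844.9 + 536.5 = 1670.4 kJ. With fibre at 8 kJ/g, add 2.3 × 8 = 18.4, giving 1688.8 kJ. The stated 1674 kJ is reproduced within 1%.
- HF: 6.13 × 17 + 22.31 × 17 + 94.83 × 37 = 3992.19 kJ, against 3992.08 stated.
- Control relative to HF: energy 1674/3992.08 = 0.42; fat 14.5/94.83 = 0.15; carbohydrate 49.7/22.31 = 2.23.

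The control is a substantial meal, not a near-fasting condition.

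**2. Clock time and fed state.** For the first participant of the day, the control-day measurements fall at 7.30 (fasted), 12.00 (3 h after the meal) and 15.00 (6 h after the meal). The later two are 4.5 h and 7.5 h after baseline, and both are fed.

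**3. Can the two effects be separated on control days?** Let μ be the fasted baseline mean, c3 and c6 the time-of-day changes, and m3 and m6 the responses to the control meal.

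- Mean at -1.5 h = μ
- Mean at 3 h = μ + c3 + m3
- Mean at 6 h = μ + c6 + m6

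There are five parameters and three means, and the design matrix has rank 3. Any amount can be moved from c3 to m3, or from c6 to m6, without changing a fitted value. Only the sums are estimable.

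**4. Do the HF days help?** Adding HF responses h3 and h6 gives seven parameters and rank 5, so c3 and c6 remain unidentified. The difference between HF and control days at 3 h is (c3 + h3) − (c3 + m3) = h3 − m3. Time of day cancels, but what remains is HF relative to breakfast, not relative to fasting.

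**5. Does the protocol's own time course help?** Section 6.1.1 says that in previous studies the FMD response was maximal at 3 h and had returned to normal by 6 h. If that is carried over to the control meal, so that m6 = 0, then c6 becomes estimable for FMD. There are then four parameters (μ, c3, c6, m3) and still rank 3, and c3 and m3 stay inseparable. The statement covers FMD only, not arterial stiffness or iontophoresis.

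**The case against.** The strongest reply is that nothing planned rests on this phrase. Circadian rhythm is not an objective (Section 2), a research question (2.1), an outcome (6.1) or an analysis (8). The control days also serve to quantify variation, and Section 8 plans an analysis for that. This stands, and it is why the point is minor. It does not make the stated use attainable.

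A second reply is that normal circadian rhythm loosely means the usual course of a day that begins with breakfast. That is a possible reading, since the shake is modelled on an average breakfast, but the protocol does not say so. If it is the intent, the rewording simply states it.

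A third is the 6 h argument in step 5. It has force for FMD at 6 h, if the control meal follows the cited time course. It does nothing for 3 h or for the other measures.

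A reader might also look to the 1.5 h offset between the two daily slots to separate clock time from meal. It does give fasted readings at 7.30 and 9.00. But the meal moves with the slot, and the protocol does not say how slots are allocated or whether a participant changes slot, so a comparison by slot may only compare different men. Reaching the 4.5 h and 7.5 h changes would need extrapolation.

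**Conclusion.** The circadian purpose in Section 3.1 is wrong as written. The control-day change in EF is breakfast response plus time of day, and the design does not separate them, most clearly at 3 h. This rests on the meal schedule, the absence of an unfed day and the protocol's premise that nutritional challenges impair postprandial EF.

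The size of the meal part cannot be given. A reader might scale the HF planning effect by the composition of the shake, but the ratio runs from 0.15 (fat) through 0.42 (energy) to 2.23 (carbohydrate), a nearly fifteenfold spread, and nothing in the protocol supports any one of them.

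A reader might also infer that the HF effect will be understated. That would require the control-day profile to be used to correct the HF days. No such correction is planned: Section 3.1 rules out direct comparison, and the primary contrasts in Section 8 are over time (3 versus 0 h and 6 versus 3 h). Nor are the control days without use, since they still inform variation. Severity is minor. The primary HF contrasts, visits and sample size stand.

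**What to change.** In Section 3.1, replace the circadian purpose with: *the time course of EF after an average breakfast (meal response and time of day combined)*. State that no circadian conclusion will be drawn from these days. Keep the statement that the triplicates quantify variation.

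Add that any reading of the HF days against the control days is relative to a normal breakfast, not to fasting. This also matters for Section 8, which plans to compare incremental areas under the curve between meals for secondary variables.

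The cost is a few sentences and the loss of the circadian claim. Meals, visits, participant numbers and primary analysis do not change.
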